**Fig. 1 Fig1:**
[figure not shown]
Schedule of enrolment, interventions and assessments

The fourth and final stage in t0 is a standard audiological examination at the ENT-clinic at the University Hospital of Giessen and Marburg (UKGM). There are two main purposes for this visit: The first is to rule out possible non-subjective causes of tinnitus, and the second, to acquire audiometric data. At the clinic, participants first learn about the components of the audiological examination before signing the informed consent form (see Additional file 5). Subsequently, the audiological examination, in which the below information is acquired, takes place:
Standard Audiogram (to 20.000 Hz)TympanometryOtoacoustic emission (OAE)Tinnitus loudness discomfort levelTinnitus matching (loudness, pitch)

Participants who are included after the visit to the ENT clinic take the baseline assessment in the pre-allocation (t1) stage. Upon completion of this assessment, participants move to the allocation (t1) stage and are randomly assigned to one of three arms in the study: Group 1, which receives alpha/delta neurofeedback training; Group 2, which receives beta/theta neurofeedback; and Group 3, which is the diary control group.

The post-allocation (t2) intervention period lasts 4 weeks. Within this timeframe, ten neurofeedback training sessions are undertaken for the two neurofeedback groups, with a minimum of two and maximum of three sessions per week. For the diary control group, two face-to face visits to the department and two telephone calls are scheduled within the 4-week period. t2 mid-point assessments are completed 2 weeks after the start of the intervention. In the post-allocation (t3) stage, participants complete the endpoint assessment online prior to a visit to the Department of Psychology, where they complete the ANT and SART (referred to as cognitive assessment II in Fig. 1). t3 post-assessments are completed 4 weeks after the start of the intervention.

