The t4 follow-up takes place 4 months after the start of the intervention. Here, participants in the neurofeedback groups complete assessments online before coming to the Department of Psychology for a booster neurofeedback session. The booster sessions serve the practical goal of probing the participants about their experiences with neurofeedback. Moreover, the visit is included to increase the likelihood of participant adherence to questionnaire completion. For diary control participants, t4 assessments are completed 4 months after the start of the intervention. As a token of appreciation, they then receive a copy of a self-help book on tinnitus [29].

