To ensure blinding of neurofeedback trial participants, two identical neurofeedback training protocols were developed. First, information about the course of the training is kept identical for participants in both groups. Second, the position of the training electrodes is the same; that is, positions FC1, FC2, F3 and F4 of the 10/10 International system were used in the training sessions. Third, the duration and intensity of the training sessions are identical for both groups; that is, all participants undergo ten sessions, each initially consisting of four but progressing to five training blocks per session. Fourth, the neurofeedback training stimulus used, i.e., a fish swimming vertically across the screen, is the same for both groups. In other words, all variables are kept constant except for the trained frequency bands, which is information not accessible to participants.

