### Adverse events

Neurofeedback is generally considered safe and involves no risk to participants [60]. This is perhaps best reflected in the fact that it has been used extensively in studies involving children with ADHD. Thus, participants in our trial should not experience more serious side effects than perhaps mild headaches, stemming mainly from the prolonged period of sustaining attention during training. Nevertheless, the adverse effects of neurofeedback training will be routinely monitored as part of the ongoing dialogue between data collectors and trial participants. In the unlikely event that a trial participant complains about serious adverse effects as a result of the training, data collectors will, as a first step, reduce the frequency of training sessions in the week of the complaint and, if needed, reduce the number of training segments per training session until the trial participant no longer complains about adverse effects.

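### The first stated response to a complaint of serious adverse effects is reduced but continuing training, with no hold or assessment before the next session

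*Protocol article*

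**What the plan says.** The Adverse events section of the protocol article expects little trouble: participants "should not experience more serious side effects than perhaps mild headaches". Adverse effects are to be "routinely monitored as part of the ongoing dialogue between data collectors and trial participants".

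It then gives a rule for the unexpected case. If a participant "complains about serious adverse effects as a result of the training, data collectors will, as a first step, reduce the frequency of training sessions", the cut applies in the week of the complaint. If that is not enough, data collectors also "reduce the number of training segments per training session until the trial participant no longer complains about adverse effects".

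The planned exposure is given elsewhere in the article. Under Procedure/trial protocol, "ten neurofeedback training sessions are undertaken for the two neurofeedback groups, with a minimum of two and maximum of three sessions per week". At the four-month follow-up, "participants in the neurofeedback groups complete assessments online before coming to the Department of Psychology for a booster neurofeedback session". Under Randomisation, "all participants undergo ten sessions, each initially consisting of four but progressing to five training blocks per session".

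**The concern.** The rule names a trigger (a complaint of serious effects attributed to the training), an actor (data collectors) and a first action (fewer sessions that week). That action keeps the suspected cause in place at a lower amount. Nothing in the article puts a pause or a review before the next session. For the second action, the only stated end point is that the participant stops complaining.

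Reducing the amount of training is sensible for a headache brought on by sustained attention. It is a poor default for a worse effect whose nature is unknown when the rule applies. Two features of this trial add some weight. The Introduction says that no tinnitus neurofeedback study has yet used the beta/theta protocol, so one training arm has no safety record in this population. It also lists despair, hopelessness, anxiety and depression as common in distressed tinnitus patients, and for effects of that kind the absence of complaint is weak evidence of recovery.

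What is at stake is the safety of individual participants: a data collector who follows the sentence exactly could train someone again before anyone has assessed the effect.

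**Working it through.** The plan gives no figure on this point, so there is none to reproduce. The check has a textual part and a count of sessions.

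**1. The text.** The steps of the rule are:
- Trigger: a complaint of serious adverse effects from the training.
- First step, by data collectors: fewer sessions, limited to the week of the complaint.
- Second step, if needed: fewer segments per session, lasting until complaints cease.
- Hold before further training: none stated here or elsewhere in the article.
- Assessment before further training: none stated here or elsewhere in the article.

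The condition that complaints cease attaches most directly to the second step. The first step has its own limit, the week of the complaint.

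**2. How much training can follow a complaint.** Inputs from Procedure/trial protocol: 10 sessions, 4 weeks, 2 or 3 sessions per week.

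Let *a* weeks have two sessions and *b* weeks have three. Then *a* + *b* = 4 and 2*a* + 3*b* = 10, so *a* = 2 and *b* = 2. The number of week orders is C(4,2) = 6. With 10 sessions after which a complaint could arise, there are 6 × 10 = 60 positions.

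*Same week, assuming a cut of one session* (the article does not give the size of the cut):
- After session 1 of a three-session week, one further session is still given: 2 per schedule × 6 = 12 of 60 (20%).
- After session 2 of a three-session week or session 1 of a two-session week, the only remaining session is removed: 4 × 6 = 24 of 60 (40%).
- After the last session of a week, nothing is left to cut: 4 × 6 = 24 of 60 (40%).

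So in 48 of 60 positions (80%) there is no further training that week.

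*Later weeks, even if the rest of the complaint week is cancelled:* each week holds 60 / 4 = 15 positions, so weeks 1 to 3 hold 45 of 60 (75%), all with training still scheduled. Summing the sessions left after the complaint week over these positions:
- Week 1: 9 × 7 + 6 × 8 = 111.
- Week 2: 3 × (4 + 5 + 5) + 2 × (6 + 5 + 5) = 42 + 32 = 74.
- Week 3: 3 × (3 + 2 + 2) + 2 × (2 + 3 + 3) = 21 + 16 = 37.

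The total is 222 and the mean is 222 / 45 = 4.93 sessions, with a range of 2 to 8. The booster comes on top.

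**3. What a missed session costs.** The Interventions section adds the extra block from session 6, so the plan is 5 × 4 + 5 × 5 = 45 blocks. One missed session is 4/45 = 8.9% or 5/45 = 11.1% of that person's training.

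**4. Who could still benefit.** Trial status gives a recruitment start of 1 November 2018, an expected end in June 2020 and a version date of 17 March 2020. The two training arms have 2 × 40 = 80 participants. Assume even recruitment to 1 June (578 days, 76 remaining) or to 30 June (607 days, 105 remaining):
- Still to start: 80 × 76/578 = 10.5, or 80 × 105/607 = 13.8.
- In their four weeks of training at that date: 80 × 28/578 = 3.9, or 80 × 28/607 = 3.7.

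**The case against.** The strongest reply turns on one word. The same section contrasts serious effects with mild headaches, so the term may be comparative: complaints somewhat worse than a headache. For those, fewer sessions and then fewer segments is an ordinary tolerability ladder, and the rule would be loosely worded rather than unsafe. That reading is plausible. But the article does not define the term, and as written the rule also covers effects for which a ladder is wrong.

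A second reply is that causality review, escalation, reporting and stopping rules belong in the full protocol, which is not at hand, and that calling something a first step implies later ones. This stands for everything that might come alongside or afterwards. It does not change which action the article puts first.

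Third, the counts measure schedule positions, not harm. No event rate is given, and in most positions the cut works as a pause for the rest of that week. The later-week figure ignores the possible segment reduction. The training is EEG recording with on-screen feedback, and neurological conditions and severe mental health issues are exclusion criteria. All of this stands and limits the weight of the point.

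Fourth, few participants remain to benefit. Ethics and dissemination has data collection ending in late spring 2020, which would leave fewer still.

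**Conclusion.** The point holds as a correction to the stated order of steps: for a complaint of serious effects attributed to training, the article puts reduction first and places no hold or assessment before further training. If no one intervenes, 75% of complaint positions lead to later-week training under the planned schedule. That figure assumes the 2-or-3-per-week pattern and weights positions equally; it is not a probability that anyone is harmed.

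Three stronger readings are tempting and are not supported:
- A reader might infer that all reduced training continues until the participant falls silent. The wording ties that condition to the segment reduction, while the frequency cut is tied to one week.
- A reader might infer that the trial handles regulatory serious adverse events by dose reduction. The article does not use the term in that defined sense.
- A reader might infer that nobody is notified and nothing is ever assessed. The article does not say so, and the full protocol may provide for it.

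The event is expected to be rare. The case for change rests on the possible consequence of a single event and on how little the change costs.

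**What to change.** Amend the Adverse events section so that:
- A serious complaint holds all further training, including the booster. Examples are a seizure-like event, marked worsening of mood or of tinnitus, or any effect that needs medical attention or persists beyond the day of the session.
- The hold lasts until the principal investigator, with medical advice where needed, has reviewed the complaint and documented whether training resumes, resumes at a reduced amount or stops.
- Reduction of frequency and segments is kept for tolerability complaints such as headache.
- A safety hold does not by itself count as a visit-schedule deviation for the per-protocol exclusion under Statistical analysis. The present rule carries the same risk: one session fewer in a two-session week leaves one, below the stated minimum of two.

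The cost is a short wording change, some review time, and a delayed or missed session (4 or 5 of 45 blocks) for the few affected. It needs no new committee or visit, and the ENT clinic that already examines participants is one possible source of medical advice. If the change counts as substantial, Ethics and dissemination requires ethics approval before it takes effect. At the version date, on the even-recruitment assumption, it would reach about 11 to 14 training-arm participants still to start, about 4 in training, and those with a booster outstanding. The time taken for approval would lower these numbers.

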### Ethics and dissemination

Should any future modification to the protocol occur that changes the study objective, design or procedures, this change will be addressed by the study’s principal investigator. Substantial protocol amendments are submitted to and approved by the responsible ethics committee, prior to implementation.

Dissemination of results is expected to follow the completion of data collection, scheduled to last until late spring in 2020. The results of the primary outcome measures are reported and disseminated, regardless of the direction and magnitude of effect(s). No restrictions are imposed on which results can be disseminated from either the trial sponsor or other interested parties.

### Statistical analysis

Data will be analysed primarily in the intention-to-treat (mITT) population. Supportive analyses are planned in the per-protocol (PP) population. mITT comprises all randomised patients, while PP analysis assesses mITT patients who show no change in their status during the trial period that violates the criteria for their inclusion/exclusion (for example, the data from someone seeking another type of treatment for their tinnitus during the trial period is excluded from further analyses).In addition, data from participants who deviate significantly from the visit schedule are excluded from analyses, and data from participants who show poor compliance during feedback sessions are excluded (e.g., showing sleepiness or lack of focus and orientation to the task). For all outcome measures, we will probe the longitudinal course across all assessments using a linear mixed model for repeated measures (MMRM, see [61]). The MMRM model includes fixed effects for group (ADR vs. TBR vs. diary control), time and group-by-time interaction, as well as a random intercept for subject specific effects using maximum likelihood estimation, adding sex, age, baseline tinnitus severity scores and patients’ expectations as covariates. The error variance-covariance matrices for the repeated factor will be specified in accordance with the data. The pattern of missing data is assumed to be random.

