### Inclusion and exclusion criteria

Participants are eligible for inclusion if they meet the following criteria:
Age + 18 yearsChronic, subjective tinnitus with a duration of ≥ 6 monthsAt least mild tinnitus distress, corresponding to a score of ≥ 18 on THI [24]Signed informed consent

The study’s exclusion criteria are as follows:
Objective tinnitus, either vascular or non-vascular in originAcute inflammatory disease of the ear/earsConductive hearing lossBlockage of the ear canal by, for example, cerumen, where removal is not desired by the individualAny current treatment for tinnitusSevere mental health issues (moderate/severe depression, bipolar disorder, psychosis)ADHDCurrent use of a psychotropic drug for a mental health conditionSubstance abusePrevious or current neurofeedback treatmentPrevious or current neurological conditions (e.g., a history of seizures, brain tumour, haemorrhage/stroke).

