#### Measures

##### Primary outcome measures

There are two primary outcome measures in the study. First, the change in tinnitus distress following neurofeedback training is measured with the THI [24]. The THI is a 25-item self-report instrument. Each item is rated on a three-point Likert scale with responses of ‘Yes’ = 4 points, ‘Sometimes’ = 2 points, and ‘No’ = 0 points, thus yielding a total score between 0 and 100. The instrument has three subscales, assessing functional, emotional and catastrophic reactions to tinnitus. The overall test-retest reliability of the scale is 0.92 [46]. It has been translated and validated into a German version [47, 48], which is used in the present study.

To assess the efficacy of neurofeedback training in reducing the perceived intensity, i.e., the sound perception of tinnitus, the TMI is used [49]. This is a three-item measure designed to assess the individual perception of tinnitus sound intensity, without overlapping significantly with cognitive, behavioural or emotional reactions to tinnitus. The internal consistency of the scale is excellent, with Cronbach’s α = 0.86; it also has satisfactory discriminant validity (correlation of *r* = .62 with the THI). One obstacle in the development of the TMI, noted by Schmidt and Kerns [49], is the differential scaling of its three items. This has, according to the authors, the potential to increase measurement error. Schmidt and Kerns [49] suggested converting the three items into a standardised scale. Consequently, in the present study, the response scales for all three items are standardised to a range from 0 to 100.

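### The per-protocol rule does not exempt THI ≥ 18, so read literally it drops participants whose primary outcome improves below the entry threshold

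*Protocol article*

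**What the plan says.** All references are to the protocol article.

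- **Statistical analysis, primary set.** The main analysis uses the set labelled mITT, and "mITT comprises all randomised patients".
- **Statistical analysis, supportive set.** "Supportive analyses are planned in the per-protocol (PP) population". Membership is defined as follows: "PP analysis assesses mITT patients who show no change in their status during the trial period that violates the criteria for their inclusion/exclusion". One illustration is given: "for example, the data from someone seeking another type of treatment for their tinnitus during the trial period is excluded from further analyses".
- **Inclusion and exclusion criteria.** There are four inclusion criteria: age, tinnitus duration of at least 6 months, at least mild distress "corresponding to a score of ≥ 18 on THI", and signed consent. The THI criterion carries no time point here.
- **Primary outcome measures.** "the change in tinnitus distress following neurofeedback training is measured with the THI". The TMI is the other primary outcome.
- **Procedure/trial protocol.** "t3 post-assessments are completed 4 weeks after the start of the intervention", which is the primary time point given in the Abstract.
- **Randomisation.** The lowest severity stratum is THI 18–36. The same section mentions the THI entry criterion again, there in terms of the score before the intervention.

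**The concern.** The rule carries the inclusion criteria, as well as the exclusion criteria, forward through the trial. One inclusion criterion is a threshold on a primary outcome, and the trial's hypotheses are that this outcome will fall. A participant who enters in the mild stratum at THI 26 and scores 12 at week 4 no longer meets the threshold. Applied as worded, the rule removes that person from the per-protocol set for having improved.

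Membership would then depend on the post-randomisation value of a primary outcome. The loss falls on participants with low follow-up scores, and more heavily on whichever arm lowers THI more. The supportive analysis would understate a real difference for reasons unrelated to adherence or protocol conduct, which are what a per-protocol analysis is meant to examine.

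**Working it through.** **Step 1: which inclusion criteria can change during the trial?** Age cannot come to be violated, and duration does not shorten while tinnitus persists. Consent can be withdrawn. The THI score can fall below 18. Apart from consent, THI is therefore the main inclusion criterion to which an in-trial change of status can apply.

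**Step 2: how much improvement triggers removal?** Each of the 25 THI items scores 0, 2 or 4, so totals move in steps of 2 and the first total below 18 is 16.

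- Entry at 18: 18 − 16 = 2 points, which is one item moving one step.
- Entry at 36, the top of the mild stratum: 36 − 16 = 20 points.

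**Step 3: how large could the effect be?** The plan states no figure on this point to reproduce, and it gives no THI mean, SD, correlation or expected change. Every distributional input below is an assumption. In both illustrations baseline THI is normal, truncated to 18–100. Follow-up is clipped to 0–100, and participants with follow-up THI < 18 are removed.

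*Illustration A.* Baseline mean is 35, 42 or 50 before truncation, SD 18 or 20, and baseline/follow-up correlation r is 0.70 or 0.85. Follow-up = mean + r × (baseline − mean) − fall + error, with error SD = SD × √(1 − r²). Falls in the better and the other arm are 10 and 3, 15 and 7, or 20 and 10 points. The contrast is the unadjusted difference in mean change.

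| Mean, SD, r | Falls | Removed (better / other) | Contrast, all → retained | Shrinkage |
|---|---|---|---|---|
| 35, 18, 0.70 | 15 / 7 | 34% / 18% | 7.7 → 6.2 | 19% |
| 42, 18, 0.70 | 15 / 7 | 24% / 11% | 7.8 → 6.6 | 15% |
| 50, 18, 0.85 | 10 / 3 | 7% / 3% | 7.0 → 6.7 | 5% |

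Over all 36 scenarios, 7–47% of the better arm and 3–24% of the other are removed, and the contrast shrinks by 5–19%.

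*Illustration B.* Baseline mean is 35, 45 or 55 and SD 18. Follow-up = baseline + arm mean change + error with SD 13. Mean changes for ADR/BTR/diary run from −12/−6/−3 to −20/−10/−5. The contrast is ADR minus BTR, adjusted for baseline.

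- Removed: about 12–46% of ADR, 7–27% of BTR and 5–18% of diary participants.
- Shrinkage of the contrast: about 12–28%.
- Example, mean 45 with −15/−8/−4: 25%, 15% and 11% are removed. Of 40 per arm that is 40 × 0.25 = 10, 40 × 0.15 = 6 and 40 × 0.11 ≈ 4 participants. The contrast moves from −6.8 to −5.4, a loss of 1.4/6.8, or about one fifth.
- No change in any arm: about 4–12% per arm are still removed, but equally, and the contrast stays at zero.

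In every scenario with a difference between arms the direction is the same: more are removed from the better arm, and the contrast moves towards zero. Together the two illustrations span roughly 5–28%.

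**The case against.** The strongest reply is that the plan does not mean this.

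- The Randomisation section describes the THI criterion in terms of the pre-intervention score, and a week-4 score cannot violate a criterion on a pre-intervention score.
- The only example in the definition is an intercurrent event. The neighbouring exclusions concern visit schedule and session compliance. Improvement is the hypothesised effect and is not naturally called a violation.
- Inclusion/exclusion is a stock pairing, and a full list of deviations would normally sit in a document that is not shown here.

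Much of this stands as evidence of intent, and a reader should not infer that the authors planned to drop improvers. It does not settle the wording. The pre-intervention phrase occurs in the rationale for stratification, and the per-protocol definition does not refer to it. The example itself takes a criterion assessed at entry, the exclusion for current tinnitus treatment, and applies it again during the trial. That is exactly the operation that would catch THI. It is offered as an example and does not close the list. The point is also not about missing detail: the article states a rule, and the rule as stated reaches too far.

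Two stronger readings are tempting, and the documents support neither.

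- *The rule also removes the worst PHQ-9 outcomes.* Moderate/severe depression is an exclusion criterion and PHQ-9 is a secondary outcome, but no text says that PHQ-9 defines the criterion.
- *The per-protocol result could contradict a true positive primary result.* This has not been shown. In the example of Illustration B the contrast keeps its sign and about four fifths of its size, and no power or significance was computed.

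That the set is no longer a randomised comparison is true of any per-protocol set defined by post-randomisation events, so it is not held against this rule in particular.

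**Conclusion.** Wrong as written, low severity. The definition does not exempt the one inclusion criterion that is itself a primary outcome, so literal application selects the set on that outcome and attenuates any real between-arm difference in THI.

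The direction follows from the rule whenever one arm lowers THI more than another. The size, roughly 5–28%, rests wholly on assumed THI distributions and arm effects. The gap between the two illustrations (5–19% and 12–28%) shows how much it depends on them. Both apply the rule at a single follow-up visit. Only the supportive analysis is touched. The primary analysis keeps everyone randomised, and no conclusion about its validity follows from this point.

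**What to change.** In the per-protocol definition under Statistical analysis:

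1. State that THI ≥ 18 is judged at entry only and never removes a participant from the set afterwards. If depression severity is assessed by a symptom score, say the same of it.
2. Limit in-trial exclusions to events that are not trial outcomes, such as starting another tinnitus treatment.

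This costs one or two sentences. It needs no new data and no change to the primary analysis. The per-protocol set can only stay the same size or grow. If the authors always meant intercurrent events alone, the change merely records what they intended.

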### Limitations

The intent-to-treat statistical method applied in the study is particularly vulnerable in relation to treatment adherence and drop-out. The willingness of participants to complete all outcome measures, independent of their status in the trial, is crucial to avoid the distortion of study results. To maximise treatment adherence and minimise drop-out in the present study, based on recommendations in the literature (e.g., [43–45]), several steps have been taken to minimise the risk.

The non-blinding of therapists in the neurofeedback conditions mean the outcomes are more susceptible to the experimenter effect. This term covers situations in which the experimenter, with awareness of the components of interventions, unconsciously or unwittingly behaves in ways towards participants that promote the favoured hypotheses [74]. To address this as best we could, a protocol containing standardised verbal instructions has been developed and used. Therefore, although the experimenter effect cannot be eliminated in its entirety, we hope this strategy, at best, minimises its impact. Regardless, the randomised controlled study design without blinding has its pitfalls, potentially influencing outcomes. Therefore, it must be considered a limitation in the study.

In conclusion, with our study we hope to take the first steps in understanding factors that promote and/or underpin reported health benefits in tinnitus populations who undergo neurofeedback treatment.

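### The sentence excluding off-schedule and poorly compliant participants names no analysis set, and its compliance rule can act only in the two neurofeedback arms

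*Protocol article*

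**What the plan says.** All in the protocol article.

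- **Primary set** (Statistical analysis): "Data will be analysed primarily in the intention-to-treat (mITT) population", and "mITT comprises all randomised patients".
- **PP set** (same section): analyses in it are supportive. Its definition is that "PP analysis assesses mITT patients who show no change in their status during the trial period that violates the criteria for their inclusion/exclusion". The one example is a participant who seeks another tinnitus treatment.
- **Further exclusions** (next sentence): "In addition, data from participants who deviate significantly from the visit schedule are excluded from analyses". The second clause of that sentence treats inattentive trainees likewise: "data from participants who show poor compliance during feedback sessions are excluded (e.g., showing sleepiness or lack of focus and orientation to the task". Neither clause names an analysis set.
- **Who has feedback sessions** (Procedure/trial protocol): "ten neurofeedback training sessions are undertaken for the two neurofeedback groups, with a minimum of two and maximum of three sessions per week". The diary arm has two visits and two telephone calls instead.
- **Blinding** (Limitations): "The non-blinding of therapists in the neurofeedback conditions mean the outcomes are more susceptible to the experimenter effect". The same section describes the method as intent-to-treat.

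**The concern.** Two separate things are at stake.

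The first is who enters the primary analysis. The exclusion sentence follows the PP definition but is not tied to it, and the mixed-model description that comes next covers all outcome measures without naming a set either. The label adds to the doubt: the primary set is called intention-to-treat but abbreviated mITT, which usually signals that someone has been left out. An analyst could apply the exclusions to the primary analysis and cite this sentence in support.

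The second holds whichever set is meant. Poor compliance in feedback sessions can be seen only where there are feedback sessions. A rule that removes drowsy or inattentive trainees from two arms and nobody comparable from the third no longer compares like with like. The contrast affected, both neurofeedback arms against diary, is one of the two purposes that the Discussion gives for the three-arm design.

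**Working it through.** **Step 1. Which set does the sentence govern?** Two readings are possible.

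- *PP only.* The sentence continues the PP definition as a list of further criteria. The PP example itself speaks of exclusion from further analyses in general terms, so the unqualified word for analyses in the next sentence need not mean every analysis. This reading agrees with the all-randomised definition and with the intent-to-treat statement in Limitations.
- *All analyses.* The sentence is a general rule. The wording allows this, but the rule then contradicts both of those statements.

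The text does not settle the matter. The conflict with the primary set is conditional.

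**Step 2. In which arms can each rule act?**

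| Rule | ADR | BTR | Diary |
|---|---|---|---|
| Departure from visit schedule | 10 sessions | 10 sessions | 2 visits, 2 calls |
| Poor compliance in feedback sessions | possible | possible | cannot occur |

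The schedule rule can act in all three arms, although ten sessions give more room to deviate. The compliance rule cannot act in the diary arm. No diary-completion rule stands beside it, although the Diary control group section says that adherence to the diary is a worry.

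**Step 3. The plan's own sample size.** Inputs from Study Design: f = 0.25, power 0.80, alpha 0.05, 3 groups, 3 measurements. For the repeated-measures MANOVA interaction (Pillai trace), s = 2, df1 = 4, df2 = 2(N − 3), λ = N·s·f². At N = 98, df2 = 190, λ = 98 × 2 × 0.0625 = 12.25 and power is 0.8005, so the stated 98 reproduces. With 120 recruited and 20% dropout, 120 × 0.8 = 96 remain and power is 0.79.

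**Step 4. Numbers lost if the primary set were affected.** Let e be the share of the 80 neurofeedback participants removed (assumed). The set becomes 120 − 80e. With 20% dropout in every arm it becomes 64(1 − e) + 32.

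**Step 5. Selection.** Suppose that those removed would have had outcomes d SD worse than those kept (assumed), with no true effect. The retained neurofeedback mean then moves by b = e·d. For pooled neurofeedback against diary, without dropout, SE = √[1/(80(1 − e)) + 1/40]. The two-sided type I error is 1 − Φ(1.96 − b/SE) + Φ(−1.96 − b/SE).

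For e = 0.20 and d = 0.8: b = 0.16, SE = √(1/64 + 1/40) = 0.202, b/SE = 0.79, error = 0.125.

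| e | Removed | Left of 120 | After 20% dropout | Power | Type I error, d = 0.25 / 0.5 / 0.8 |
|---|---|---|---|---|---|
| 5% | 4 | 116 | 92.8 | 0.78 | 0.050 / 0.052 / 0.055 |
| 10% | 8 | 112 | 89.6 | 0.76 | 0.052 / 0.057 / 0.069 |
| 15% | 12 | 108 | 86.4 | 0.74 | 0.054 / 0.066 / 0.092 |
| 20% | 16 | 104 | 83.2 | 0.72 | 0.057 / 0.079 / 0.125 |

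The power column matters only if the rule reaches the primary set. The error columns apply to whichever set it governs. For ADR against BTR, equal exclusions with equal prognosis largely cancel. If they fell on ADR alone, the error would lie between 0.05 and 0.104 over the same range.

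**The case against.** The strongest reply is that this is a drafting ambiguity and no more. The primary set is expressly all randomised patients, Limitations stresses that outcomes be completed whatever a participant's status in the trial, and the exclusion sentence sits where further PP criteria would sit. Much of this stands. A reader might infer that the plan removes people from its primary analysis, but the documents do not show that.

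Three further inferences also go beyond the text.

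- *Unblinded trainers decide who is excluded.* The trainers run the sessions and the therapists are unblinded, so this is likely. No assessor is named, however, and Training outcomes gives the trainers only the monitoring of learning.
- *The PP status rule drops responders whose THI falls below the entry score of 18.* The entry criteria do contain that score, but the rule speaks of a change in status and its only example is seeking other treatment. Nothing suggests that a better outcome score is meant to count.
- *Thresholds for schedule deviation and compliance are missing.* An article may leave those to the full protocol or analysis plan, so their absence is no finding.

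It can also be said that PP sets are selective by nature and that this one is only supportive. That lowers the stakes but does not answer the second half of the point. The compliance rule is stated, not omitted, and what it states applies to two arms of three. Confining it to PP leaves that asymmetry in place.

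**Conclusion.** The point holds in two parts. The plan does not say which set its exclusions govern; on one of two available readings they contradict the all-randomised primary set. On either reading, the compliance rule selects on subjective behaviour after randomisation that can arise only in ADR and BTR, probably judged by people who know the arm. Neurofeedback against diary is therefore open to bias in the set concerned whenever compliance is related to outcome.

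The size cannot be fixed from the documents. Over the assumed ranges it runs from negligible (0.01 SD, type I error 0.05) to material (0.16 SD, 0.125). The direction, favouring neurofeedback, rests on the further assumption that inattentive trainees do worse, which the documents do not state. Severity is moderate: the more natural reading spares the primary analysis, but the other reading would change who is in it.

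**What to change.** 1. State that the schedule and compliance exclusions define the supportive PP set only, and that every randomised participant stays in the primary analysis as allocated. Call that set intention-to-treat and drop the mITT abbreviation.
2. For PP, replace the judgement of sleepiness and focus with objective adherence criteria that have an equivalent in each arm, such as sessions attended and diary days completed. Have them applied before outcomes are seen, by someone unaware of arm.
3. As a minor clarification, say that the PP status rule refers to events such as starting another treatment and not to on-study outcome scores.

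The cost is a few sentences. The planned sample size does not change. The PP set becomes slightly larger and less selected, so it describes well-engaged trainees less purely.
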